### **Fidelity**

Fidelity is the degree to which the intervention was implemented as specified in the protocol (Proctor et al., 2011). It will be indicated by patient and provider adherence to core components of the intervention. Thresholds for success, from T1 to T3, are: 90% patient completion of the I-Score prior to meeting with the physician; 90% provider review of the patient’s I-Score results prior to or during the clinic visit.

### **Objective 2 -Evaluate the implementation strategy**

Evaluation of the implementation strategy will be performed in relation to the same constructs as for the first objective. However, the assessment of acceptability, appropriateness, and fidelity will be solely based on analysis of qualitative data (see Table 2). As to feasibility, it will be assessed in terms of the rate of technical issues encountered and recorded in the Application Manager’s notes, and the percentage of providers who participated in the implementation activities (i.e. education meeting, focus groups), with a success threshold set at 80% or more.

### **Objective 3 -Determine preliminary intervention and effectiveness outcome utility**

This pilot study will collect data on one service outcome, patient management. It will be verified with a checklist submitted to participating physicians to allow them to record, per patient encounter, if they received the I-Score results on time, if they reviewed them prior to or during the clinic visit, if they were discussed during the visit, and if the I-Score identified concerning barriers. Then, they will check off any clinical actions that were taken based on the I-Score results or any related patient-provider discussion (e.g., recording issues in medical notes, referring to another health professional, ordering a test, changing a medication or treatment, providing advice or education). See the Appendix for the physician checklist.

The patient outcomes assessed in this pilot are barriers to adherence, adherence and viral load. Barriers to ART adherence will be assessed at T1, T2, and T3, with our previously described ePROM. Adherence will be examined with the Self-Rating Scale Item (SRSI) (Feldman et al., 2013) at T1, T2, and T3. It is a one item measure of treatment adherence (i.e. “Rate your ability to take all your medications as prescribed” [over the past 4 weeks], rated on a 6-point scale (i.e. Very poor, Poor, Fair, Good, Very good, and Excellent). Viral load, a clinical indicator of viral activity (e.g., infectiousness) and treatment response, will be treated as a dichotomous variable based on whether, as indicated in the patient’s medical file, the HIV RNA viral load is detectable (over 50 copies), or not. Undetectability is a goal of HIV treatment. The most recent viral load test result at T1 and T3, will be collected.

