**Methods:** This 6-month study will adopt a one-arm mixed method type 3 implementation-effectiveness hybrid design and be conducted in a single clinical site, the Chronic Viral Illness Service of the McGill University Health Centre. It will be guided by tools of implementation science (e.g., frameworks, outcomes). Five HIV physicians and 30 of their HIV patients will participate. The intervention will involve having patients complete the I-Score with an adapted version of the Opal smartphone app, prior to meeting with their physician. Both the patient and the physician will have access to the I-Score results, for consideration during the clinic visits at Time 1 (T1), T2 (3 months), T3 (6 months). The implementation strategy will focus on patient and provider involvement, education, and training, as well as on promoting the intervention's adaptability. The strategy's cornerstone will be the hiring of an Application Manager to facilitate implementation. Implementation, patient, and service outcomes will be collected (T1, T2, T3). The primary outcome of this pilot study is the intervention's acceptability (target: mean scale score of 4 on 5). Qualitative data obtained through provider focus groups (T2, T3), patient interviews (T2, T3) and the Application Manager's field notes (T1-3) will serve especially to evaluate the implementation strategy and inform any methodological adaptations.

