### Setting and participants

The study setting is a large hospital-based clinic in Montreal, Quebec, Canada. This clinic, the Chronic Viral Illness Service (CVIS) of the MUHC, offers multidisciplinary care to approximately 2000 adults living with HIV. Five physicians treating individuals with HIV at the CVIS will be recruited to participate as well as 30 of their adult patients. This sample size amply meets rule of thumb recommendations for one-arm pilot studies (Sim & Lewis, 2011). Patients must be confirmed HIV-positive, have a history of known or suspected adherence problems in the past year, be aged at least 18 years old, be on or beginning combination ART, be literate in English or French, and own a smartphone. Full details on eligibility are presented in the next section. Ten female patients will be recruited, to ensure sufficient representation of women living with HIV (Public Health Agency of Canada, 2018).

[figure not shown]

Figure 3. Pilot study design.

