#### Inclusion criteria

- be aged 18 years or older
- be diagnosed with HIV-1 infection
- be treated with a combination antiretroviral therapy (composed of 2 to 3 different drugs)
- have had known or suspected adherence problems in the past 12 months based on a detectable viral load test result per local standards, patient report, and/or report by the healthcare team (by the physician, nurse, social worker or pharmacist)
- be treated for HIV at the Chronic Viral Illness Service of the McGill University Health Centre
- be able to speak and understand either French or English
- possess a smartphone with an appropriate data plan and/or home Wi-Fi connection

- be willing to download the smartphone app

Patients many not participate if they...

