
### *Data collection*

#### *Quantitative component*

The quantitative component will have three sources of data: 1) participant self-report; 2) electronic medical records; and 3) passive data (e.g., on app use to assess fidelity). At T1, T2 (3 months) and T3 (6 months), a study questionnaire will be administered to participants online or, if needed, with a hardcopy, especially to assess implementation outcomes.

At T1, the questionnaire will also ask about socio-demographics (e.g., year of birth, preferred language, sex, sexual orientation, ethnic group identity, immigration, education, income) and digital technology use as well as pose general health questions for patients (year of diagnosis with HIV, treatment satisfaction) and clinical practice questions for physicians (years practicing in HIV, current number of HIV patients). The measures of digital technology use are as follows: frequency of mobile device use (adapted from Schnall et al., 2018), having a health app on one's mobile device (Mahmood et al., 2019), extent of health app use (adapted from Balapour et al., 2019), confidence in reporting medical information using mobile technology (Balapour et al., 2019), and intention to report personal health data with a mobile device app, if asked by a provider (Balapour et al., 2019). All of this information will help contextualize the findings and describe the sample (see the Appendix for the patient and physician questionnaires). Clinical data, namely, HIV viral load in copies/mL, to determine viral suppression, will be extracted from patients' medical health record at the clinic, at T1 and T3.

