### *Feasibility*

Feasibility relates to the extent to which our I-Score intervention is successfully used or carried out within the study site (Proctor et al., 2011). To determine feasibility, data will be collected on the Consent rate, defined as the proportion of approached eligible patients and physicians who consent to participate. Individuals who choose not to participate will be asked to provide select sociodemographic information (sex, year of birth, preferred language) and their reason(s) with a checklist on a refusal form (see the Appendix). If 70% or more agree to participate, the study will be judged feasible on this aspect. We will also examine the Retention rate, indicated by the proportion of patients and physicians who complete the study. Eighty percent will be considered the benchmark for success. Missing I-Score data rates due to network failure as well as patient and provider non-completion of self-reported questionnaire data will be calculated as well. The criterion for success on this metric is at least 90%. Furthermore, participants will complete the Feasibility of Intervention Measure (Weiner et al.,

2017), at T1, T2 and T3, a four-item self-report measure that is appropriate for different stakeholder groups (e.g., patients, providers). Example items include “This [evidence-based practice] seems possible” and “This [evidence-based practice] seems doable.” Average scores of at least 4, indicative of agreement on the 5-point response scale, will signify the I-Score intervention’s feasibility.

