Regarding the patient outcomes of Objective 3, barriers to adherence and adherence will be summarized with the minimum, the maximum, the mean, and the standard deviation. Viral load will be reported by absolute and relative frequencies, as it is considered a dichotomous variable. For the service outcome obtained from the physician checklist, we will report the proportion of clinic visits when physicians took action based on the I-Score results, among the visits where an adherence barrier of concern was identified by physicians. Proportions will be reported for T1, T2 and T3 and globally, across time periods. To evaluate evidence of a statistically significant difference in our chosen effectiveness outcomes, we will run a Student's paired t-test for barriers to adherence and adherence and a McNemar test for viral load, between T1 and T3. To complete the analysis of the service outcome, we will use a logistic regression model, considering only the visits where an adherence barrier of concern was identified by physicians. The dependent variable is the binary variable of whether or not an action was taken by physicians and the independent variable is the time, considered as a factor with three independent levels (T1, T2 and T3). We will test the null hypothesis that time has no effect on the probability of taking action, with a t-test on the regression coefficient. We will conclude the analysis by testing the null hypothesis of equality of proportions between all pairwise combinations of time points, with a Student's t-test between two proportions, performing a Bonferroni correction for multiple tests. For all analyses, a significance level of 5% will be adopted.

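### Viral load is extracted in copies/mL but analysed only as above or not above 50 copies, so changes on one side of 50 count as no change and the power of the T1–T3 test is unplanned

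*Protocol*

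**What the plan says.** Under Data collection, Quantitative component, the protocol states: "Clinical data, namely, HIV viral load in copies/mL, to determine viral suppression, will be extracted", at T1 and T3. Under Objective 3 the outcome becomes binary, according to whether "the HIV RNA viral load is detectable (over 50 copies), or not", and the reason given is that undetectability is a goal of treatment. Under Quantitative analysis: "Viral load will be reported by absolute and relative frequencies, as it is considered a dichotomous variable". The T1–T3 comparison is a McNemar test, version not named, and "For all analyses, a significance level of 5% will be adopted". Table 3 gives p ≤ 0.05 as the threshold for success for viral load.

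On entry, the Inclusion criteria ask for evidence or suspicion of poor adherence during the preceding year, which can be established by any of several routes: "based on a detectable viral load test result per local standards, patient report, and/or report by the healthcare team". On size, the Summary says "Five HIV physicians and 30 of their HIV patients will participate", justified under Setting and participants only by "This sample size amply meets rule of thumb recommendations for one-arm pilot studies". There is no power calculation for viral load.

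**The concern.** Once the value is cut at 50, the size of any change is lost. A fall from 100,000 to 60 copies is log10 5.00 to 1.78, a drop of 3.22, and it is scored as unchanged. A move from 49 to 51 is a rise of 0.017 log10, and it is scored the same as full rebound.

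McNemar's test uses only patients who cross the line, and only those above 50 at T1 can cross it downwards. Because a patient can enter without a detectable result, the number able to improve is left to chance.

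Objective 3 asks whether the intervention shows promise and whether the chosen outcomes are useful. With p ≤ 0.05 as the mark of success, a non-significant result could be read as evidence against viral load as an outcome for the definitive trial. The cut, or a small number of viraemic patients, could produce that result even if viral load fell substantially.

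**Working it through.** The protocol states no figure for this outcome, so there is none to reproduce.

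**Inputs from the protocol.** n = 30. The retention benchmark ("Eighty percent will be considered the benchmark for success") gives 0.80 × 30 = 24. Alpha is 0.05; sidedness is not stated, so two-sided is assumed.

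**Inputs assumed, because the protocol gives none.** d = share detectable at T1; s = share of those suppressed by T3; r = share of the undetectable who rebound, set at 5%.

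**Step 1: what McNemar needs.** Let b be the number moving from above to not above 50, and c the reverse. Exact two-sided p = min(1, 2 × P[Bin(b + c, ½) ≤ min(b, c)]).
- 5:0 gives 2/32 = 0.0625.
- 6:0 gives 2/64 = 0.031.
- 7:1 gives 2 × (1 + 8)/256 = 0.070.
- 8:1 gives 2 × (1 + 9)/512 = 0.039.

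The uncorrected chi-square version, (b − c)²/(b + c), is more lenient: 4:0 gives 4.0, p = 0.046. The continuity-corrected version gives p = 0.041 at 6:0.

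**Step 2: power over the plausible range.** (b, c) is trinomial with p10 = d × s and p01 = (1 − d) × r. Summing over all pairs with p ≤ 0.05:

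| d | s | Exact, n = 30 | Exact, n = 24 | Uncorrected, n = 24 |
|---|---|---|---|---|
| 20% | 50% | 3% | 1% | 9% |
| 30% | 50% | 14% | 7% | 24% |
| 50% | 30% | 17% | 9% | 30% |
| 50% | 50% | 58% | 41% | 62% |
| 70% | 50% | 91% | 79% | 90% |
| 100% | 50% | >99% | >99% | >99% |

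The answer depends mainly on d and s, and the protocol fixes neither.

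**Step 3: what the numeric values would add.** Assume k viraemic patients with T1 log10 uniform on 2–5, falls with mean 1.0 and SD 0.8, values floored at 50 (log10 1.70), and one further patient who rebounds. Under these inputs about 26% of viraemic patients cross 50. With one rebound, exact McNemar needs at least 8 crossings, so its chance of p ≤ 0.05 is P[Bin(k, 0.26) ≥ 8]. The signed-rank figures are simulated.

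| k | Exact McNemar | Signed-rank, rebound to 200 copies | Signed-rank, rebound level uniform on log10 2–5 |
|---|---|---|---|
| 8 | about 0% | about 55% | about 13% |
| 10 | about 0.1% | about 77% | about 32% |
| 12 | about 0.4% (0.2–0.6% across simulations) | about 90% | about 73% |

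A separate simulation used a paired t-test on log10 copies: n = 30, detectable T1 values normal with mean 3.5 and SD 1, undetectable set to 1.6, fall 1.0 with SD 0.8, 5% rebound. It points the same way, exact McNemar against the t-test: 2% v 50% with 30% detectable, 11% v 86% with 50%, 35% v 99% with 70%.

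**Step 4: limits of the alternative.** Patients at or below 50 at both times have zero difference and drop out of the signed-rank test. With five non-zero differences, all falls, its smallest exact two-sided p is 2/32 = 0.0625, the same floor as exact McNemar at 5:0.

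**The case against.** The binary outcome is deliberate and consistent throughout the protocol. Undetectability is the stated goal, copies are extracted in order to determine suppression, and a fall from 100,000 to 60 is not suppression. Viral load is one of three patient outcomes under a secondary objective of a small pilot whose hybrid design only observes effectiveness. The primary outcome is acceptability. A supportive analysis might also sit in a statistical analysis plan that is not at hand. The first part stands, and it is why the binary outcome should stay. The last part does not remove the point, because the protocol positively states that viral load is reported as frequencies on the ground that it is dichotomous.

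Three stronger readings are tempting, and the documents do not support them.
- *The entry cut-off differs from 50.* The inclusion criterion refers to local standards and gives no number, so it could be 50. It is also one of three entry routes, looks back 12 months and is not the T1 value. A patient detectable then can be undetectable at T1 even with identical cut-offs.
- *The test has almost no ability to show a signal.* That is true only if few are viraemic or few become suppressed. In the Step 3 set-up with a mean fall of 2.0 log10, about 56% cross 50 and exact power is 33%, 69% and 96% for 12, 15 and 20 viraemic patients.
- *With five or fewer detectable patients it can never show improvement.* That holds for the exact test only. The protocol does not name the version, and the uncorrected one reaches 0.046 at 4:0.

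**Conclusion.** The point holds as a minor one. The protocol gathers viral load on a continuous scale and specifies only a binary analysis, judged by p ≤ 0.05. Its power was never planned: near zero when few patients are detectable at T1 or few become suppressed, and about 80–90% when 70% are detectable and half of those become suppressed. In the scenarios run with a real fall and 8–12 viraemic patients, the log10 analysis was much more sensitive, roughly 13–90% against less than 1%. The range reflects the number viraemic and the size of a single rebound. With five or fewer informative patients, neither exact test can reach 0.05.

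All of these figures rest on assumed detectable shares, suppression and rebound rates, and log10 changes, because the protocol gives none. What needs no assumption is that changes on one side of 50 contribute nothing to the planned test, and that the number of patients able to improve is not controlled.

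**What to change.** Keep the proportion above 50 and the McNemar test. Add to Quantitative analysis, as supportive:
- the T1–T3 change in log10 copies/mL, with values at or below 50 set to 50, compared by a paired signed-rank test;
- the two discordant-pair counts alongside the McNemar result;
- a listing of T1 and T3 values for every patient above 50 at either time.

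State that a non-significant McNemar result will be read together with the number detectable at T1, and not taken alone as evidence that viral load is an unhelpful outcome.

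The cost is wording only: the values are already to be extracted, and no visit, assay or procedure is added. The downside is one more exploratory analysis, on data censored at 50 and of little use if five or fewer patients are informative.

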## **Data analysis**

### **Quantitative analysis**

Time 1 questionnaires for people living with HIV and for HIV physicians will be summarized with descriptive statistics. For continuous variables, the minimum, the maximum, the mean, and the standard deviation will be reported. For ordinal and nominal qualitative variables, we will report absolute and relative frequencies (proportions).

As, specified, for most quantitative metrics relating to Objectives 1 and 2, as recommended for pilot studies, score targets were set to evaluate the ability to proceed to a definitive trial (Thabane et al., 2010). For people living with HIV and HIV physicians, continuous outcomes expressed on a Likert scale will be summarized with the minimum, the maximum, the mean, and the standard deviation at T1, T2 and T3. Binary outcomes (yes or no) will be reported with absolute and relative frequencies (proportions) at T1, T2 and T3. The means and proportions of T1, T2 and T3 will be confronted with their corresponding thresholds for success, presented in Table 2. To study the tendency of means and proportions for people living with HIV over time, a Linear Mixed Model (LMM) or a

Generalized Linear Mixed Model (GLMM) will be used, for continuous and binary outcomes, respectively. The response variable of each model will be the corresponding outcome and the independent variable will be the time (T1, T2 and T3). The null hypothesis of no time effect on the corresponding outcome will be tested with a Student's t-test on the regression coefficient. If the null hypothesis is rejected, we will perform post-hoc Student's paired t-tests between all combinations of time points to show between which time points means and proportions differed significantly. Additionally, to verify if each threshold for success is met at the end of the study, we will test the null hypothesis that each mean or proportion at T3 is inferior to its corresponding threshold with a Student's t-test. For all analyses, a significance level of 5% will be adopted. Finally, where appropriate, Cronbach's alpha will be calculated to evaluate the internal consistency of subscales.

Regarding the patient outcomes of Objective 3, barriers to adherence and adherence will be summarized with the minimum, the maximum, the mean, and the standard deviation. Viral load will be reported by absolute and relative frequencies, as it is considered a dichotomous variable. For the service outcome obtained from the physician checklist, we will report the proportion of clinic visits when physicians took action based on the I-Score results, among the visits where an adherence barrier of concern was identified by physicians. Proportions will be reported for T1, T2 and T3 and globally, across time periods. To evaluate evidence of a statistically significant difference in our chosen effectiveness outcomes, we will run a Student's paired t-test for barriers to adherence and adherence and a McNemar test for viral load, between T1 and T3. To complete the analysis of the service outcome, we will use a logistic regression model, considering only the visits where an adherence barrier of concern was identified by physicians. The dependent variable is the binary variable of whether or not an action was taken by physicians and the independent variable is the time, considered as a factor with three independent levels (T1, T2 and T3). We will test the null hypothesis that time has no effect on the probability of taking action, with a t-test on the regression coefficient. We will conclude the analysis by testing the null hypothesis of equality of proportions between all pairwise combinations of time points, with a Student's t-test between two proportions, performing a Bonferroni correction for multiple tests. For all analyses, a significance level of 5% will be adopted.

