## Study metrics and instruments

Details on the constructs assessed; the instruments and metrics used; the chosen thresholds for success, if applicable; the participant group contributing data; and the timing of data collection are presented in Table 2. Many of the chosen metrics are based on those recommended by Stover et al. (2020). Importantly, the authors emphasize the need to standardize evaluation metrics in patient-reported measure implementation and to distinguish between those used to assess perceptions of the innovation and those used to assess the implementation strategy. Not meeting the set thresholds for success, in this study, will signify that modifications are necessary before proceeding to a definitive trial (Thabane et al., 2010).

Table 1. Schedule of study procedures for participants

| Procedure                                                  | Timeline               |                        |                        |                        |
|------------------------------------------------------------|------------------------|------------------------|------------------------|------------------------|
|                                                            | Prior to study start   | Study start (baseline) | Month 3                | Month 6                |
| Be screened and/or consent                                 | Patients
Physicians |                        |                        |                        |
| Attend educational meeting                                 | Physicians             |                        |                        |                        |
| Receive training on the I-Score measure and Opal           | Patients
Physicians | Patients
Physicians | Patients
Physicians | Patients
Physicians |
| Complete the I-Score measure via Opal                      |                        | Patients               | Patients               | Patients               |
| Examine the I-Score measure results via the ORMS dashboard |                        | Physicians             | Physicians             | Physicians             |
| Attend HIV patient-physician visit (online or in person)   |                        | Patients
Physicians | Patients
Physicians | Patients
Physicians |
| Complete the post-visit checklist                          |                        | Physicians             | Physicians             | Physicians             |

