## Objective 1 -Evaluate perceptions of the I-Score intervention

### *Acceptability*

The primary outcome of this pilot study will be acceptability, as measured by the Acceptability E-scale (AES) for web-based PROMs (Tariman et al., 2011). *Acceptability* is related to how agreeable, palatable, or satisfactory an intervention is perceived to be by stakeholders (Proctor et al., 2011). It will be measured, at T1, T2, and T3, with an adapted version of the AES for administration to both patients and physicians in the study. The scale has 6 items rated on a 5-point Likert scale that varies depending on the item. Example items of the original measure include “How would you rate your overall satisfaction with this computer program?”, and “How easy was this computer program [...] for you to use?” A summary score is obtained by adding the item scores (range: 6-30). A score of at least 24 (80% of maximum) indicates high acceptability and usability, as suggested by the scale developers.

Acceptability will also be measured at T1, T2 and T3 with a variant of the Net Promoters Score (NPS) used by England’s National Health Service (NHS) and labelled the Friends and Family Test (NHS, 2014). The NPS is considered a measure of user satisfaction (Hamilton et al., 2014). A single question will be asked (“How likely are you to recommend the I-Score?”) and rated on a 5-point Likert scale (1 = Extremely unlikely, 2 = Unlikely; 3 = Neither likely nor unlikely; 4 = Likely; 5 = Extremely likely). From this measure, the percentage recommending the I-Score will be calculated (score of 4 or 5), with a success threshold of 80% or more. An NPS-type score will also be calculated by creating three groups: promoters (score of 5), passives (score of 4), and detractors (score of 1-3). Subtracting the percentage of detractors from the promoters provides the NPS. NPS scores range from -100 to 100. A positive score (> 0) will be considered good (Stirling et al., 2019), and a score of  $\geq 50$ , excellent.

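### The protocol sets two pass rules for the same success thresholds: they disagree just above the target, and for some proportions the tested rule cannot be passed at all

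*Protocol*

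**What the plan says.** The target appears in three places with no test or confidence bound attached. The Summary gives it as "target: mean scale score of 4 on 5". The Acceptability section under Objective 1 says: "A score of at least 24 (80% of maximum) indicates high acceptability and usability". Table 3 lists a mean of at least 24 for patients and physicians at T1, T2 and T3. The other Objective 1 and 2 targets have the same form: means of at least 4 or 5.5, proportions of at least 70%, 80% or 90%, and a Net Promoter Score above 0.

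The Quantitative analysis section does two things with these targets.

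- It compares values at all three times: "The means and proportions of T1, T2 and T3 will be confronted with their corresponding thresholds for success, presented in Table 2". (The thresholds stand in the table captioned Table 3; the citation of Table 2 is a cross-reference slip.)
- Later in the same paragraph it adds that, "to verify if each threshold for success is met at the end of the study, we will test the null hypothesis", the null being that "each mean or proportion at T3 is inferior to its corresponding threshold". The level is 5%; sidedness is not stated, though the null is directional.

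Study metrics and instruments gives the consequence: "Not meeting the set thresholds for success, in this study, will signify that modifications are necessary before proceeding to a definitive trial".

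**The concern.** Both comparisons are attached to the same question, whether the threshold is met. One asks whether the value reaches the target. The other asks whether the T3 value is significantly above it, which requires clearing the target by a margin that grows with the SD and shrinks with the sample size. A result inside that margin is a success under one sentence and a failure under another.

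The pilot's main product is the decision whether to go to a definitive trial unchanged. If the primary outcome lands just above its target, that decision is undefined, and someone would have to choose the rule with the data in view. The sample size of 30 and 5 rests on a rule of thumb for pilots and no power is stated for these tests, so a failure under the tested rule may reflect sample size and not poor acceptability.

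**Working it through.** **The plan's own figure.** 0.80 × 30 = 24, and 6 items × 4 = 24. The Summary, the Acceptability section and Table 3 give the same target.

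**Inputs.** 30 patients and 5 physicians (Summary); target 24; level 5%, taken as one-sided because the null is directional. The protocol gives no SD for the E-Scale, so 3, 4 and 5 points on the 6–30 scale are assumptions. The 80% retention benchmark (Feasibility) leaves 0.80 × 30 = 24 patients.

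**Means.** The observed rule passes at 24.00 or more. The tested rule passes when the observed mean exceeds 24 + t(0.95, n−1) × SD/√n. For n = 30, t = 1.699; at SD 4 this is 24 + 1.699 × 4/√30 = 25.24.

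| Assumed SD | Mean needed, n = 30 | Mean needed, n = 24 | Pass chance at true mean 25, n = 30: observed rule | Same: tested rule |
|---|---|---|---|---|
| 3 | 24.93 | 25.05 | 96.6% | 55.5% |
| 4 | 25.24 | 25.40 | 91.5% | 37.9% |
| 5 | 25.55 | 25.75 | 86.3% | 28.3% |

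The observed-rule chance is from the normal distribution and the tested-rule chance from the noncentral t. Read two-sided, the tested limits at n = 30 rise to 25.12, 25.49 and 25.87.

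Example: T3 mean 25, SD 4, n = 30. The observed rule is met. The test gives t = (25 − 24)/(4/√30) = 1.37, one-sided p = 0.091, so it is not met.

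Outside the band the rules agree. Below 24 both fail; above the tested limit both pass. At a true mean of 26 (SD 4, n = 30) the pass chances are 99.7% and 84.8%.

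**Proportions.** No SD has to be assumed here.

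- *Five physicians, 80% threshold* (for example, the share likely to recommend the I-Score). 4/5 = 80% meets the observed rule. Under the t-test, 4/5 gives t = 0, and 5/5 has zero variance so t is undefined. An exact test at 5/5 gives 0.8^5 = 0.328. No result passes.
- *24 retained patients, 90% threshold* (I-Score completed on time, taking the 24 patients seen at T3 as the denominator). 22/24 = 91.7% meets the observed rule. For 23/24 the proportion is 0.958 with standard error 0.0417, so t = 0.0583/0.0417 = 1.40 on 23 degrees of freedom, one-sided p = 0.087. For 24/24 t is undefined, and the exact p is 0.9^24 = 0.080. No result passes.
- *All 30 patients.* At 80% the observed rule needs 24/30 and the t-test 27/30. At 90% they need 27/30 and 29/30. Here the tested rule is stricter but can be passed.

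**The case against.** The best reply is that the paragraph can be read as one rule. The comparison at three times closes a block of descriptive statistics and states no consequence. Only the later sentence speaks of verification, and it fixes the time point, null, test and level. On that reading nothing is left to choose after the data are seen. A target for a mean is also compatible with testing the mean against it.

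This carries some weight: the comparison sentence alone could be descriptive. It does not settle the matter. The Summary, the Acceptability section and Table 3 all define success by the value reached. Where Table 3 means a significance criterion it says so: the Objective 3 rows carry p ≤ 0.05 in the same threshold column where Objectives 1 and 2 carry plain values. And if the test is the only rule, some listed thresholds cannot be met by any result.

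It is also fair that the test sentence follows time modelling restricted to patients, so its use for physicians is an inference from its reference to each mean or proportion. If physicians were excluded, the two groups would be judged by different rules, which the protocol does not say.

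Two stronger readings are tempting and not supported. A reader might infer that the rules contradict each other across the plausible range; they do so only in a band above the target whose width depends on an assumed SD. A reader might also infer that the test puts the physician mean targets almost out of reach. With n = 5 and an assumed SD of 3 the E-Scale mean needed is 26.86 of 30, which is demanding but attainable. Impossibility applies to certain proportions, not to the means.

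Finally, missing a threshold leads to modifications, not abandonment, and the results are read alongside qualitative data. That limits the harm but does not say which rule triggers the modifications.

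**Conclusion.** The point stands in this form: the protocol fixes two pass rules for the same thresholds, ranks neither, and ties progression to the outcome. For the patient E-Scale with 30 patients, one-sided, they give opposite verdicts when the T3 mean falls between 24.0 and about 24.9 to 25.6 (SD 3 to 5, assumed). At a true mean of 25 and SD 4 the verdicts would differ in about 91.5% − 37.9% ≈ 54% of such pilots; that figure belongs to one chosen true mean and is not a general rate. The result for proportions is firmer because it needs no SD: with five physicians at 80%, or with 24 patients as the T3 denominator at 90%, the tested rule fails even perfect performance. This is a contradiction in the protocol's own text, not detail left to an analysis plan, and it should be resolved before analysis.

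**What to change.** State one rule, in both Study metrics and instruments and Quantitative analysis:

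- A threshold is met when the observed value in the given participant group, at the timing listed for that metric in Table 3, is at or above its target (above zero for the Net Promoter Score), reported with a 95% confidence interval, exact for proportions.
- For questionnaire metrics collected at T1, T2 and T3, including the E-Scale, the T3 value decides; T1 and T2 are descriptive.
- Consent, retention, missing data, fidelity and participation in implementation activities keep their own listed period. A blanket T3 rule would not fit them: consent is collected at T1 only, and the educational meeting takes place before study start.
- Report the E-Scale verdict separately for patients and physicians, and state in advance either that the patient result decides the primary outcome or that both must pass.
- Keep the T3 test, if at all, as supportive, not as the verifier of the threshold. Correct the table citation at the same time.

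The cost is a few sentences; design, data collection and targets do not change. The downside should be named: an observed-value rule passes about half the time when the true mean is exactly at the target, and about 25% of the time at a true mean of 23.5 (SD 4, n = 30: −0.5/(4/√30) = −0.68). That is why the confidence interval must accompany every verdict.
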